**Patients and Methods:** This open-label randomized clinical trial will be conducted at the Department of Otorhinolaryngology and Head Neck Surgery in collaboration with the Department of Virology and Department of Medicine in Dhaka Medical College Hospital (DMCH). The study will be conducted from September 2020 to December 2020. A total of 189 confirmed cases of COVID-19 disease proven by reverse transcription polymerase chain reaction (RT-PCR) testing will be enrolled in this study. Written informed consent will be ensured before participation. In case of no literacy, fingerprint will be considered for written permission. Consent will be sought from the legal guardian in case of minor or underaged. Formal ethical clearance will be obtained from the Ethical Review Committee (ERC) of Dhaka Medical College (DMC). All of the participants will be divided into seven Arms: Arm 1 will receive povidone iodine (PVP-I) nasal irrigation at a concentration of 0.4%, Arm 2 and Arm 3 will receive 0.5% and 0.6%, Arm 4 will receive PVP-I nasal spray at a concentration of 0.5% and Arm 5 will receive 0.6%. Arm 6 (placebo comparator group) will receive nasal irrigation with distilled water (DW), and Arm 7 (placebo comparator group) will receive nasal spray with distilled water. The contact time will be minimum 30 seconds. After the individual application of PVP-I and distilled water in the respective participants, they will be tested again for RT-PCR for COVID-19 from nasopharyngeal samples. All patients will be subjected to a detailed history, physical examination and adverse events. Computer generated randomization sequence will be followed for randomization. Data will be recorded in a semi structured questionnaire and will be analyzed by ‘R-4.0.2’ data analysis software.

**Conclusion:** It is expected that the study will reveal the virucidal activity with optimal contact time and concentration of nasal preparations of PVP-I against COVID-19. The results may help in prevention strategies for the general population, health care workers and COVID-19-positive patients.

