**Sample size:**

- - For 80% power, Z_β_=.84
  - For 0.05 significance level, Z_α_=1.96
  - r=1 (equal number of cases and control)
  - σ=10.0
  - Difference = 5.0

Therefore, n=126

Including exclusion criteria total sample 63*2+

30*2=186.

Therefore, in each group, a total of 27 samples will be collected after randomization.

**Number of participants:** The total number of participants will be 27 in each arm (7 Arm x 27=a total of 189 sample).

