**Proposed Analysis Plan of the study:**

Data analysis will be performed by data management software, R-4.0.2’. Then, the principal investigator (PI) will also check and verify the data. Then data will be transferred to statistician. If it is consistent with the objectives, then the PI and his team will draft the final result.

The following procedure will be followed during data analysis. The RCT aims to determine whether povidone iodine can clear COVID-19 virus from the nasopharynx of COVID-19 positive patients. The analysis will be performed on an intention-to-treat basis and a per-protocol basis. Subgroup analyses based on the primary outcome will also be estimated. Although the study is not formally powered for these subgroup analyses, the analysis will be added to draw a more conclusive statement. Statistical significance is set at the 95% confidence level at the 5% acceptable error level. Differences will be considered significant at the P < 0.05 level for all these tests. The data will be expressed as the means ± standard deviations (SD) for continuous variables and as frequencies (%) for categorical variables. Chi-square test and Student’s t test or ANOVA will be used in cases of normally distributed data, and similar non parametric data will be used whenever appropriate. Data will be analyzed by SPSS 20 Windows version (Chicago, Illinois, USA), and graphs and charts will be expressed by Microsoft Excel 2016.

.

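### An unadjusted P < 0.05 for every test across five active arms, with unpowered subgroups used to firm up the conclusion, does not hold the protocol's stated 5% error level

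*Protocol*

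**What the plan says.** Protocol, Proposed Analysis Plan of the study, sets the error level: "Statistical significance is set at the 95% confidence level at the 5% acceptable error level". The next sentence gives the only decision rule: "Differences will be considered significant at the P < 0.05 level for all these tests". The tests named are chi-square, t test and ANOVA, on both an intention-to-treat and a per-protocol basis, and neither set is named as leading.

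On subgroups the same section says: "Although the study is not formally powered for these subgroup analyses, the analysis will be added to draw a more conclusive statement". It names no subgroup factor.

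Protocol, Procedure of randomization, lists seven arms: PVP-I irrigation at three concentrations, PVP-I spray at two, and one distilled-water control for each route. Sample size puts 27 participants in each arm, 189 in all.

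Protocol, Research Hypothesis, states a single hypothesis about nasal PVP-I preparations as a whole. Part-A, Conclusion, goes further: "It is expected that the study will reveal the virucidal activity with optimal contact time and concentration of nasal preparations of PVP-I against COVID-19". Claims about single concentrations are therefore intended.

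**The concern.** A 5% error level and a separate 5% threshold for each of several tests are not the same thing. With five active arms there are at least five chances to find a concentration that appears to work, and nothing in the protocol says which test decides the trial or whether one test must succeed before the others are read.

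The subgroup sentence makes this worse. Analyses that are admitted to be unpowered cannot make a conclusion firmer. They add further chances of a false positive, and their negative results carry little information.

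At stake is a claim that a particular concentration or route clears virus when it does not. Part-A, Conclusion, says the results may inform prevention for the general population and health care workers.

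This is not a detail left to a statistical analysis plan. The protocol fixes the threshold and the role of the subgroups, so an analysis plan that adjusted for multiplicity would contradict it.

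**Working it through.** **Inputs from the protocol.** Significance level 0.05 two-sided ("For 0.05 significance level, Z_α_=1.96"); power 80% ("For 80% power, Z_β_=.84"); SD 10; difference 5; equal allocation; seven arms of 27.

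**The protocol's own figure.** n per group = 2 × [10 × (1.96 + 0.84) / 5]² = 62.7, so 63 per group and 126 in total. This agrees with the Sample size section. The calculation covers one two-group comparison at 0.05, so it makes no allowance for several tests.

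**Five tests, no true effect.** The natural family is three irrigation arms against the irrigation control and two spray arms against the spray control.
- If the tests were independent: 1 − 0.95⁵ = 22.6%.
- Tests that share a control are correlated. Simulation under the normal approximation gives 20.4% to 20.5%.
- Counting only results that favour PVP-I: about 10.5%.
- With each test at 0.05/5 = 0.01: about 4.5%.

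**The same five tests with a binary RT-PCR result.** The protocol gives no clearance rate, so a range is assumed, with the same true rate in all arms and 27 per arm (200,000 simulated trials at each rate):

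| Assumed clearance | Uncorrected chi-square, any P < 0.05 | of which favouring PVP-I | Fisher's exact, any P < 0.05 |
|---|---|---|---|
| 5% | 10.0% | 5.6% | 0.4% |
| 10% | 21.1% | 10.6% | 3.3% |
| 20% | 22.8% | 11.4% | 8.5% |
| 30% | 21.8% | 10.9% | 10.8% |
| 40% | 19.1% | 9.5% | 10.8% |
| 50% | 17.3% | 8.9% | 9.3% |

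**Larger families (assumed, because the protocol lists none).**
- All 21 pairs, 7 × 6 / 2: about 44%.
- The five tests plus the same five in each half of one binary subgroup factor: about 42%. With two or three such factors: 56.5% and 66.6%.

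**Power of the alternatives at difference 5, SD 10.**
- One arm against its control: standard error 10 × √(2/27) = 2.72 and 5/2.72 = 1.84. Power by the t test is about 44% at 0.05 and about 21% at 0.01 (45% and 23% by normal approximation).
- All PVP-I (5 × 27 = 135) against all distilled water (2 × 27 = 54): standard error 10 × √(1/135 + 1/54) = 1.61, ratio 3.11, power about 87%. Stratified by route (81 v 27 and 54 v 27) the standard error is 1.62, the ratio 3.09 and the power again about 87%.

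**The case against.** The best case against the point concerns its size. Most of it stands.

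- **A false claim is not shown to be likely.** A reader might infer that a spurious finding for some concentration is more likely than not. The documents do not support that. The natural five-test family gives about 20%, and figures above 40% need pairwise tests or subgroup factors that the protocol does not list.
- **Direction.** The 20% counts errors both ways. A false result in favour of PVP-I has about a 10% chance.
- **Test version.** With a binary endpoint the figure depends on the clearance rate and on the test. At 5% clearance Fisher's test gives only 0.4%.
- **Choice of test.** A reader might also infer that the plan misuses chi-square, because the sentence continues "or ANOVA will be used in cases of normally distributed data". The wording is loose: normality most naturally belongs to the t test and ANOVA, and the same sentence allows non-parametric alternatives. A claim of small expected counts would rest on an assumed clearance rate. This is not put forward as a defect.
- **A single question is visible.** The hypothesis is about PVP-I as a whole, and the sample size compares cases with controls. That suggests a pooled test, but the plan never designates one.
- **Two analysis sets.** Planning both intention-to-treat and per-protocol analyses is usual, and the sets overlap heavily, so this adds little error.
- **A global gate.** Requiring a significant ANOVA first would hold the error near 5% when no arm works. The protocol names ANOVA but does not make it a gate.

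What remains is the stated rule itself and the role given to the subgroups. No objection touches either.

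**Conclusion.** The point holds in this form: the protocol's decision rule does not keep its own 5% error level over the comparisons it intends to interpret, and the subgroup sentence gives a confirmatory role to analyses that cannot bear it.

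For the five arm-versus-own-route-control tests the error is about four times the stated level by normal approximation (20% against 5%). For a binary endpoint it ranges from about 10% to 23% with uncorrected chi-square and from about 0.4% to 11% with Fisher's test. These figures assume no effect in any arm, 27 analysed per arm and, for the binary results, clearance between 5% and 50%. The 44% (all pairs) and 42% (one binary subgroup) illustrate families that the current wording permits but does not specify.

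The right description is a substantially inflated error rate with no designated deciding test, not a probable false claim. It should be corrected before the analysis, because the rule is written into the protocol and correcting it needs only new wording.

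**What to change.** Replace the single-threshold sentence with a fixed order:

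1. Lead test, intention-to-treat: all PVP-I arms (135) against all distilled-water arms (54), stratified by route, two-sided 0.05. This tests the hypothesis in the Research Hypothesis section.
2. Only if step 1 is significant: the five arm-versus-own-route-control comparisons, with Holm or an equivalent adjustment.
3. Per-protocol results and all other tests are supportive.

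Replace the subgroup sentence with: subgroup analyses are exploratory, are reported as treatment-by-subgroup interactions with confidence intervals, and are not used for the conclusion.

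**Cost.** No extra patients are needed. On the protocol's sample-size inputs the lead test has about 87% power. The price is paid at arm level: at the strictest Holm step (0.05/5 = 0.01) single-arm power falls from about 44% to about 21%, so claims about a single concentration will be harder to support. These powers refer to a continuous measure with difference 5 and SD 10. Power for a binary clearance endpoint would need an assumed clearance rate, which the protocol does not give. Other schemes that control the error over the five comparisons would also serve, provided one is fixed in advance.

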**Rationale of the study**

Coronavirus disease 2019 (COVID-19) is a highly infectious disease that causes human-to-human transmission primarily by respiratory droplets from coughing, sneezing and speaking. In early SARS-CoV-2 infection, a greater viral titre can be found in saliva and nasal mucous; minimization of these titres should help to reduce cross infection. Povidone-iodine (PVP-I) disinfectant has better antiviral activity than other antiseptics and has already been proven to be an extremely effective virucide in vitro against severe acute respiratory syndrome and Middle East respiratory syndrome coronaviruses (SARS-CoV and MERS-CoV). Its in vivo virucidal activity is unknown, although its nasal or oral preparation can be effective in reducing transmission. Earlier, very few studies evaluated the efficacy of povidone-iodine as a nasal antiseptic or oral rinse antiseptic against the SARS-CoV-2 virus, but the results of those studies are not undebatable. Therefore, the aim of this study was to investigate the virucidal activity of povidone iodine on coronaviruses located on the mucosal surface of the oropharynx and nasopharynx, which is very rational in this pandemic period.

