**Inclusion criteria:**

- - - - Age: 15-90 years
      - Either gender
      - Patients diagnosed with COVID-19 disease by RT-PCR
      - Have confirmed COVID-19 symptoms and symptom onset within the past 4 days
      - Capable of using a nasal spray device and perform nasal irrigation required by the study
      - Willing to participate

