**Method and data collection:**

**Participant selection and enrolment:** All patients admitted to the medical wards through the emergency department or outpatient department with suspected COVID-19 cases will be initially approached and screened for confirmation of COVID-19. Confirmation of COVID-19 will be performed by positive impression of RT-PCR results. Following confirmation of the viral infection, the patients will be seen by the ward doctors and clinical trial physicians (registered physicians). Moreover, baseline complete blood count (CBC) will be performed for each patient. Chest X-ray/high-resolution computed tomography (HRCT) will be performed in necessary cases. The ward doctors and trial physicians will together care for the patient; then, the patients will be briefed about the aim, objective and details of the procedure of the study. If without capacity, their relatives will be approached about the trial and seek their consent for recruitment. As this study will be confined to a tertiary care hospital, patients will be recruited up to day 4 of illness.

**Consenting participants:** It will be prioritized that the patients will be treated early for COVID-19 management by a standard regimen and in accordance with the guidance of the national guidelines. Within the shortest possible time, preferably within 4 hours of admission, the consenting procedure will be completed either from the patient or from the attendant/legal guardian of the patients to obtain the full potential benefit of the treatment. Written informed consent will be obtained from the patient in their own language [Bengali] by trial physicians working on the trial.

**Screening for eligibility:** During admission, demographic and clinical details, including name, age/date of birth, sex, duration of onset of fever and hospitalization, vital statistics will be recorded before randomization. RT-PCR for COVID-19 will be used for confirmation of COVID-19 virus infection. A screening log will be maintained including these essential details and the decision made by the patient, attendant or legal guardian where appropriate concerning recruitment. Ineligible and non-recruited patients will also be cared for by ward physicians following standard treatment guidelines.

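### RT-PCR clearance is to be compared by unadjusted tests although time since onset is already collected; adjusting for it would be a modest, nearly free gain in power

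*Protocol*

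**What the plan says.** Under Proposed Analysis Plan of the study, the protocol names the chi-square test for categorical data, says that Student's "t test or ANOVA will be used in cases of normally distributed data", and provides for nonparametric counterparts. Clearance is a positive or negative repeat RT-PCR, so it falls to the chi-square test in that sentence. No covariate or model is mentioned.

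Under Procedure of randomization, seven equal arms are filled from a computer-generated sequence, with no stratification factor stated. The Sample size section sets 27 per arm.

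Three other places concern time since onset:
- Method and data collection, screening for eligibility: "duration of onset of fever and hospitalization, vital statistics will be recorded before randomization".
- Inclusion criteria: "symptom onset within the past 4 days". Illness day must therefore be known for every participant.
- Rationale of the study: "In early SARS-CoV-2 infection, a greater viral titre can be found in saliva and nasal mucous".

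**The concern.** By the protocol's own account, illness day bears on how much virus is present, and the outcome is whether a swab taken within minutes of one application is still positive. A baseline value that plausibly predicts the outcome is thus in hand before randomisation, but neither the design nor the named analysis uses it. In arms of 27, chance differences in illness day add noise to each comparison. Adjustment would remove part of that noise without new patients or measurements. At stake is some power, in a trial that has little to spare for pairwise comparisons, and protection against choosing an adjustment only after baseline imbalances have been seen.

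**Working it through.** **1. The protocol's own sample size.** Inputs from the Sample size section: "For 0.05 significance level, Z_α_=1.96", "For 80% power, Z_β_=.84", SD 10, "Difference = 5.0", equal groups.

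n per group = 2 × (1.96 + 0.84)² × 10² / 5² = 2 × 7.84 × 4 = 62.72, rounded up to 63, so 126 in total. This reproduces. Then 63×2 + 30×2 = 186, 186/7 = 26.6, rounded up to 27, and 7 × 27 = 189.

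**2. Pairwise power on those inputs.** SE = 10 × √(2/27) = 2.72. Power = Φ(5/2.72 − 1.96) = Φ(−0.12), or 45%.

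If a covariate has correlation ρ with the outcome, the residual SD is 10 × √(1 − ρ²). The documents give no ρ, so a range is assumed:

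| ρ | Variance reduction | Power, 27 v 27 |
|---|---|---|
| 0 | 0% | 45% |
| 0.1 | 1% | 45.5% |
| 0.3 | 9% | 49% |
| 0.5 | 25% | 56% |
| 0.7 | 49% | 73% |

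Reaching 80% with 27 per arm would need 1 − ρ² = 27/62.72 = 0.43, or ρ of about 0.75. The protocol does not name the variable behind the SD of 10, so this step is a guide only.

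**3. Size of chance imbalance.** Assume onset uniform over days 0, 1, 2, 3, 4 (variance 2). The SD of the difference in mean onset between two arms is √(2 × 2/27) = 0.385 day.
- One arm-control pair: P(difference > 0.5 day) = 2 × [1 − Φ(0.5/0.385)] = 19%.
- At least one of the five PVP-I arms against its route-matched water arm: 61% by simulation.

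A half-day imbalance multiplies the odds ratio by exp(0.5 × slope), which is 1.16, 1.28 or 1.49 at slopes of 0.3, 0.5 or 0.8 per day. For scale, take slope 0.5 and clearance of 10% v 40% (odds ratio 6). The log odds ratio shifts by 0.25, against a sampling SE of √(1/2.7 + 1/24.3 + 1/10.8 + 1/16.2) = 0.75. The shift is one third of an SE.

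**4. Power for binary clearance.** Simulation at 27 v 27, onset uniform on 0-4, 20,000 runs per setting. Pearson chi-square is compared with a logistic score test for arm adjusted for onset day as a linear term. Control negativity, odds ratios and slopes are assumptions.

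| Log-odds slope per day | Control 10%, OR 6: chi-square → adjusted | Control 20%, OR 4.5: chi-square → adjusted |
|---|---|---|
| 0.3 | 0.75 → 0.74 | 0.70 → 0.71 |
| 0.5 | 0.69 → 0.70 | 0.64 → 0.68 |
| 0.8 | 0.60 → 0.65 | 0.53 → 0.61 |

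Before rounding, the changes are about −1 to +2, +1 to +4 and +5 to +9 points. Slope 0.8 means odds that change exp(4 × 0.8) = 24.5-fold from day 0 to day 4.

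**5. Type I error.** With no treatment effect, the chi-square test and the adjusted score test both rejected in about 5 to 6% of runs at every slope. A likelihood-ratio test is less safe here: at 10% negativity it ran at 7 to 8%, with or without the covariate. The method therefore matters as much as the covariate.

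**The case against.** **Covariates belong in a SAP.** The choice of covariates is often left to a SAP, the protocol's randomisation section refers to a statistical plan, and nothing forbids an adjusted model. This stands to the extent that silence alone would be no finding. But the protocol is not silent: it names the tests, and all are unadjusted.

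**The planned test is valid.** This stands in full. A reader might infer that any chance difference in illness day will be mistaken for a treatment or concentration effect, so that the results are biased. The documents do not support that. Randomisation makes the comparison unbiased, and the chi-square test's 5% already allows for such differences.

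**The prognostic link is thin.** The rationale speaks of titre in early infection. It gives no gradient within the first four days and says nothing about RT-PCR conversion minutes after an application. The four-day entry window narrows the covariate's range and so probably its predictive strength. The item listed at screening is onset of fever, whereas the inclusion criterion concerns symptom onset. All of this stands and keeps the expected gain modest.

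**The larger weakness is power.** Pairwise power is 45% on the protocol's own inputs, and no plausible covariate repairs that. This also stands. It limits the value of the change but is no reason to leave free information unused.

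**Conclusion.** The point holds as a modest gain in efficiency. The protocol plans unadjusted comparisons between unstratified arms of 27 while holding a baseline value that it treats as related to viral titre. With assumed slopes of 0.3, 0.5 and 0.8 per day, adjustment changes pairwise power by about −1 to +2, +1 to +4 and +5 to +9 points. It could be worth nothing if onset day is weakly prognostic within the window.

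Two stronger readings should be resisted. One is that precision is certainly and materially lost: its size depends on a slope that the documents do not give, and for a binary outcome the benefit is power, not a narrower interval on the log-odds scale. The other is that the 61% figure describes a typical comparison: it is the worst of five, and one pair has 19%. Both percentages rest on onset being uniform over days 0-4.

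**What to change.** State one main clearance analysis in the analysis plan: post-application RT-PCR negativity in each PVP-I arm against its route-matched water arm (irrigation with irrigation, spray with spray), adjusted for days since symptom onset as a linear term. Take that value from the onset date already used for eligibility, not from fever onset, and make sure that the case record form holds it for every participant.

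Fix a single method in advance that copes with sparse or zero cells and holds its type I error. One example is an adjusted score test for the P value, with Firth-penalised logistic estimates and a standardised risk difference for reporting. Do not leave a choice among logistic, penalised and exact methods to be made once the clearances are known. Keep the chi-square test as a sensitivity analysis.

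The cost is a sentence or two in the plan and slightly more analysis work, with no new patients or measurements. The downside is little or no gain if onset day proves weakly prognostic. The low pairwise power remains and must be dealt with separately.
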